### Trial design

The present randomized, double blind, placebo-controlled trial aims to evaluate the efficacy of a tDCS treatment in improving the clinical outcome of children and adolescents with AN, assessed as changes in Eating Disorder Risk composite score (EDRC) of the Eating Disorder Inventory (EDI-3).

## Materials and methods

### Study setting and participants

Eighty youth with AN will be recruited at the Anorexia and Eating Disorder simplex Unit, Child and Adolescent Neuropsychiatry Complex Unit, of the Bambino Gesù Children’s Hospital in Rome, Italy. Participants will be enrolled during the daily clinical activities of the Unit by a team of psychologists, neuropsychiatrists, and psychiatrists highly trained. Principal investigator will full inform participants and their parents about the procedures and purpose of the experiment, prior to obtain their written consent. Participation will be solely voluntary.

### Eligibility criteria

Inclusion criteria are the followings: 1. diagnosis of AN according to the Diagnostic and Statistical Manual of Mental Disorders, Fifth Edition—DSM-5 (American Psychiatric Association & American Psychiatric Association, 2013), confirmed by experienced developmental psychiatrists and psychologists through extensive clinical examination; 2. a condition of under-weight (BMI < 18.5 kg/m^2^); 3. intelligence quotient (IQ) higher or equal to 85 (IQ ≥ 85); 4. age ranging from 10 to 18 years included; 5. ability to give informed consent under parents' surveillance and guidance.

Exclusion criteria include: 1. a personal history of neurological/medical/genetic diseases; 2. a personal history of epilepsy; 3. suicide risk; 4. receiving CNS-active drug, other counseling or psychological therapies during the treatment.

### Interventions

All participants will undergo a tDCS treatment (active or sham) plus a TAU for six weeks, delivered for three times a week.

#### tDCS treatment

Participants in the active tDCS group will receive active stimulation to DLPFC via two saline-soaked, 25 cm^2^ sponges placed over F3 (anode) and F4 (cathode), according to the International 10–20 system. The current will be delivered via BrainStim stimulator (E.M.S. s.r.l.; Bologna, Italy) and will slowly increase during the first 30 s (ramp-up) to 1 mA while will decrease slowly to 0 mA during the last 30 s (ramp-down). Between the ramp-up and the ramp-down, a constant direct current (1 mA) will be delivered for 20 min, as in previous pediatrics tDCS studies [56–59]. To reduce the likelihood of irritation related to electrical stimulation, a low dose of gel cream (1/8 of an inch) will be applied on the sponges’ surface. Before tDCS application, the electrodes impedance will be checked to guarantee that it will be below 10 kΩ.

To control for any placebo effects, participants in the sham tDCS group will undergo the same procedures during the 20 min of the session, but the current will be applied for 30 s and will be ramped down without the participant’s awareness (0 mA).

To minimize any risk associated with tDCS, an experienced investigator will administer and supervise all tDCS sessions and ask the participant to report any discomfort. Stimulation stops if sensation on the scalp is uncomfortable or a headache occurs.

#### TAU

After each session of tDCS treatment, the participants will undergo TAU, including: 1. meetings for the nutritional and psychiatric monitoring for patients (once a week); 2. psychological support for patients by group sessions (twice a week, 60 min duration); 3. psychoeducation therapy for parents in group sessions (twice a week, 60 min duration).

Each session will be provided by highly trained professionals in ED (psychotherapists, psychiatrists and nutritionist), who will be blinded about the experimental conditions.

### Measures

To verify the efficacy of each condition (active or sham), a full assessment of psychological, neurophysiological and physiological measures will be carried at T0 and T1. Instead, follow-ups evaluations (T2, T3, T4, T5) will include only psychological and physiological assessment.

#### Psychological measures

Psychological measures about intellectual level [60] and socio-demographical status (parent-report questionnaire) will be collected at T0, while psychopathological measures will be collected at T0, T1 and at all follow-ups.

The psychopathological assessment of AN symptomatology will include: EDI-3 [61], which comprises 91-item that give a measure of basic ED characteristics through six composite scores [EDRC, Ineffectiveness (IC), Interpersonal Problems (IPC), Affective Problems (APC), Overcontrol (OC), and General Psychological Maladjustment (GPMC)] and nine general psychological scales [Low Self-Esteem; Personal Alienation; Interpersonal Insecurity; Interpersonal Alienation; Interoceptive Deficits; Emotional Dysregulation; Perfectionism; Asceticism; Maturity Fears]; Eating Attitudes Test (EAT-26) [62], which comprises 26-item that measures anorexia nervosa symptoms and produces a total score; and Body Uneasiness Test (BUT) [63], which contains 34-items to measures body image concerns and produces a global severity index (GSI). All questionnaires will be completed by the participants themselves.

To investigate participants’ behavioral and emotional symptoms, the Child Behavior Checklist for Ages 6–18 (CBCL 6–18) and the Youth Self-Report for Ages 11–18 (YSR 11–18) [64] will be administered, which are parental reports and self-reports questionnaires respectively. The CBCL 6–18 and YSR 11–18 questionnaires include a 113-item and 112-item scale, respectively, that produces several subscales, including syndrome scales (Withdrawn, Somatic Complaints, Anxious/Depressed, Social Problems, Thought Problems, Attention Problems, Delinquent Behavior and Aggressive Behavior, a Total Problem Score) and two broadband scores, Internalizing Problems and Externalizing Problems.

Anxiety and depressive symptoms will be evaluated through the following self-reports scales: Multidimensional Anxiety Scale for Children—second edition (MASC-2) [65] and the Children’s depression inventory—second edition (CDI-2) [66]. The MASC-2 is a 50-item self-report, which measure: Separation/Fears, Generalized Anxiety Index, Obsessions/Compulsions, Harm Avoidance, Social Anxiety (Humiliation/Rejection and Performance Fears) and Physical Symptoms (Panic and Tense/Restless). The CDI-2 is a 28-item self-report inventory that provides a Total Score and scores on two scales: Emotional Problems and Functional Problems. In addition, it provides scores for four further sub-scales, called Negative Mood/Physical Symptoms, Negative Self-Esteem, Ineffectiveness and Interpersonal Problems.

#### Neurophysiological measures

The neurophysiological measures will be collected at T0 and T1 in two separate sessions for each hemisphere respectively.

##### TMS protocols for the assessment of cortical excitability, sensory-motor integration and plasticity

Each TMS session consists of a pp-TMS and rTMS protocols. Specifically, pp-TMS protocols included short intracortical inhibition and facilitation (SICI/ICF) and short-latency afferent inhibition (SAI) with a conditioning-test design (magnetic or electric). Moreover, LTP mechanisms will be assessed in both hemispheres by rTMS, with the intermittent theta burst stimulation (iTBS) protocol. This measure allows to assess cortical excitability for each hemisphere, evaluated in terms of different motor-evoked potentials (MEPs) amplitude recorded at different time-points after rTMS perturbations. For each time point, these measures will be collected in two separate sessions, one day apart, for each hemisphere in order to avoid possible interhemispheric plasticity effects. Furthermore, iTBS protocol will be run at the end of the experimental session in order to avoid the interference of plasticity effect on other measures.

##### TMS-EEG protocol for the assessment of cortical oscillations, reactivity and functional connectivity

EEG was performed using a TMS-compatible EEG equipment (BrainAmp 32MRplus, 20 BrainProducts GmbH, Munich, Germany). In each TMS-EEG session, 80 TMS single pulses will be applied over the primary motor cortex (M1) and DLPFC of both hemispheres (320 pulses in total) at a random interstimulus interval (ISI) of 2 to 4 s, in counterbalanced order. TMS intensity will be set at 90% of the resting motor threshold (RMT) defined as the lowest intensity producing MEPs with a peak-to-peak amplitude > 50 µV in five out of 10 trials in the relaxed first dorsal interosseous muscle (FDI) of the hand [67]. TMS-evoked potentials (TEPs) will be evaluated in the spatiotemporal–domain to assess the cortical connectivity and reactivity measuring the waveform, latency, amplitude and cortical distribution of TEPs components. Moreover, the cortical oscillatory pattern will be explored with a time/frequency–domain analysis to evaluate the synchronization and desynchronization in theta, alpha and beta frequencies over motor and premotor areas.

In addition, quantitative EEG (qEEG) during resting state will be performed in an eyes-closed state at the beginning of the experimental session.

#### Physiological measures

Endogenous stress response system functioning and nutritional status will be collected at T0 and T1, as well as T2 and T4, while BMI will be assessed at each evaluation.

To investigate the endogenous stress response system functioning, the HPA axis functioning will be evaluated through the measurement of the Cortisol awakening response (CAR). To this purpose, participants will be instructed to collect saliva samples at home in two consecutive working days. They will be invited to collect saliva samples at awakening (in bed) and 15-, 30- and 60-min following awakening, by using the sampling device “Salivette” (Sarstedt; Rommelsdorft, Germany). Saliva cortisol concentrations will be measured by an enzyme immunoassay method, using a commercially available ELISA kit (Biochem Immunosystem, Milan, Italy). As measures of the CAR, the cortisol area under the curve relative to the ground (AUCg) and the AUC with respect to the increase (AUCi) will be also calculated.

The nutritional state will be evaluated by blood tests: Electrolytes, full blood count, Hematocrit, MCV, folate, B12, TIBC, albumin, transferrin, ESR, protein electrophoresis, serum total cholesterol, high density lipoproteins, triglycerides, glucose profile, glycaemia, insulin, AST, ALT, GGT, FT4, TSH, sexual hormones, cortisol, immunologic evaluation, copper.

Finally, BMI will be calculated as the person’s weight in kilograms divided by the square of height in meters.

#### Safety and tolerability questionnaire

Symptoms and side effects will be assessed using standard questionnaires [68] completed by participants after each tDCS session and at each follow-up. The questionnaire lists adverse effects, such as headache, neck pain, scalp pain, tingling, itching, burning sensation, skin redness, sleepiness, trouble concentrating, and acute mood change. Participants will quantify the intensity of the symptoms or side effects that are related to tDCS as follows: (1) absent; (2) mild; (3) moderate; and (4) severe.

To screen potential subjects for risk of adverse events during TMS, all participants completed non-invasive brain stimulation screening [69] that consists of fourteen yes or no questions, based on accepted safety considerations for TMS.

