### Participant timeline

Baseline assessment (at time 0-T0) will be completed before the interventions are administered. Participants will undertake tDCS treatments (active or sham) plus a TAU for six weeks delivered for three times a week (18 session). Participants will be evaluated at the end of the treatment (at time 1-T1) and one-month later (at time 2-T2), three months later (at time 3-T3), six months later (at time 4-T4) and one year later (at time 5-T5). In the last follow-up, participants will be asked to indicate whether they believe they were receiving active or sham tDCS.

See Fig. 1 for details on the specific assessment of each visit.

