### Blinding

The investigators, the highly trained ED professionals involved in the TAU and participants, as well as their parents, will be blinded to the group allocation. In addition, data for each measure will be collected from blinded experimenters and will be insert in electronic and protected data files.

Randomization information will be maintained until data collection is completed by an independent researcher, who will have an emergency code break envelope to open in case of serious adverse event that requires knowledge of the interventions to manage the participant’s condition.

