### Safety considerations

The risks associated with participation in the study are low. One possible critical aspect is related to the use of NIBS itself. Standard NIBS paradigms are considered safe and well-tolerated in developmental age [70] including those with underlying neurological conditions or mental disorders [71]. Safety guidelines for the application of TMS and tDCS in pediatric patients report no serious adverse events, but only mild and transient [34, 70, 72].

Previous studies conducted by our laboratory [40, 56–59, 73] have also demonstrated the safety and tolerability of tDCS and its usefulness in improving cognitive and psychopathological measures in children and adolescents with developmental and psychopathological disorders.

Adverse effects will be registered during the total time of the study, using a standard questionnaire [68, 69]. The experimenter will follow participants for adverse effects even after the end of the study.

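### The side-effect rating is worded as limited to symptoms related to tDCS, with only the blinded participant to judge; every listed symptom should be rated whatever its cause

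*Protocol article*

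**What the plan says.** All references are to the protocol article.

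- **Safety and tolerability questionnaire**, instrument and timing: "Symptoms and side effects will be assessed using standard questionnaires [68] completed by participants after each tDCS session and at each follow-up". The list has ten items: headache, neck pain, scalp pain, tingling, itching, burning, and then "skin redness, sleepiness, trouble concentrating, and acute mood change".
- **Same section**, scoring: "Participants will quantify the intensity of the symptoms or side effects that are related to tDCS as follows", with the grades "1) absent; (2) mild; (3) moderate; and (4) severe".
- **Blinding**: "participants, as well as their parents, will be blinded to the group allocation".
- **Participant timeline**: 18 sessions, then follow-ups at one, three, six and twelve months. Only at the last of these, "participants will be asked to indicate whether they believe they were receiving active or sham tDCS".
- **Safety considerations**: "Adverse effects will be registered during the total time of the study, using a standard questionnaire". This carries no relatedness limit. It cites the same questionnaire and, with it, the reference used elsewhere for the TMS screening questions.
- **tDCS treatment**: at each session the investigator will "ask the participant to report any discomfort".

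**The concern.** The scoring sentence ties intensity to causality. As worded, the quantity recorded is not whether a symptom occurred and how strongly, but how strong it was if it came from tDCS. The only person named to make that judgement is a participant aged 10 to 18 who does not know whether current was given.

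For scalp tingling or skin redness under the electrode this hardly matters. Four of the ten items are different. Headache, sleepiness, trouble concentrating and acute mood change can plausibly come from the illness, undernutrition or ordinary life. A child who blames one of these on something other than stimulation could, following the sentence literally, mark it absent. At follow-up, one month to one year after the last session, the attribution is harder still.

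A sham-controlled trial does not need this filter to deal with background symptoms. Randomisation makes the background comparable in the two arms, so a difference in all-cause rates can be read directly as an effect of active current. Restricting the record to attributed symptoms puts a subjective judgement between the event and that comparison. What is at stake is the sensitivity of the tolerability record in minors to brief, non-specific effects after a session.

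**Working it through.** **Step 1. Does the text impose a relatedness condition?** The scoring sentence does, in so many words. The sentence that introduces the questionnaire does not: it has symptoms and side effects assessed without qualification. The grade absent fits both readings. It could be the grade for a listed item that did not occur, or for one that occurred but was not put down to tDCS. The wording is therefore open to two readings, and one of them discards data.

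**Step 2. Is there a scored record elsewhere without the condition?**

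| Place | Relatedness limit | Scored separately? |
|---|---|---|
| Safety and tolerability questionnaire | yes, as worded | four grades per item |
| Safety considerations | none stated | no; points back to the same questionnaire |
| tDCS treatment | none stated | no; a verbal check during stimulation |

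No other place in the article describes a separate, unfiltered, graded record of these symptoms.

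**Step 3. How large could the effect be?** The article states no adverse-effect rate and no between-arm test of adverse effects, so there is no figure of the plan's own to reproduce. The only input from the document is n = 40 per arm. All rates below are assumptions, chosen to show direction and range.

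Let p1 and p0 be the true rates in the active and sham arms, and a the share of symptoms attributed to tDCS, equal in both arms. The recorded rates are a·p1 and a·p0. With r1 and r0 for the recorded rates:

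SE = √[r1(1−r1)/40 + r0(1−r0)/40], z = (r1−r0)/SE, power ≈ Φ(z − 1.96).

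| True rates | a | Recorded rates | SE | z | Power |
|---|---|---|---|---|---|
| 40% v 20% | 1 | 40% v 20% | 0.100 | 2.00 | 52% |
| 40% v 20% | 0.5 | 20% v 10% | 0.079 | 1.26 | 24% |
| 40% v 20% | 0.3 | 12% v 6% | 0.064 | 0.94 | 15% |
| 30% v 15% | 1 | 30% v 15% | 0.092 | 1.63 | 37% |
| 30% v 15% | 0.5 | 15% v 7.5% | 0.070 | 1.07 | 19% |
| 30% v 15% | 0.3 | 9% v 4.5% | 0.056 | 0.80 | 12% |

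With equal attribution the ratio of rates stays at 2 throughout. The absolute difference and the chance of seeing it shrink. The contrast is diluted but not reversed.

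**Step 4. Attribution that differs by arm.** This needs blinding to fail, at least in part. Assume a true rate of 30% in both arms, attribution of 80% among those who guess active and 40% among those who guess sham.

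- *Partial failure* (60% of the active arm and 40% of the sham arm guess active). Active: 0.30 × (0.6×0.8 + 0.4×0.4) = 0.192. Sham: 0.30 × (0.4×0.8 + 0.6×0.4) = 0.168. The difference is 2.4 points with SE 0.086, so z = 0.28. A 5% two-sided test rejects with probability Φ(−1.68) + Φ(−2.24) ≈ 6%.
- *Complete failure* (every participant guesses correctly). Recorded rates are 0.30×0.8 = 24% and 0.30×0.4 = 12%, a false difference of 12 points.

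A spurious arm difference is thus negligible under modest unblinding and becomes material only if blinding largely breaks down.

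**The case against.** The strongest reply is that the filter may not exist. The phrase about relation to tDCS can simply describe the list, six of whose ten items (neck pain, scalp pain, tingling, itching, burning, redness) are mainly local or sensory. Nothing says that the child first judges causality or that an unrelated symptom goes ungraded. The form itself is a cited standard questionnaire that is not shown, and it may already record intensity and relatedness separately. This stands as a reason not to assert that data will be lost. It does not remove the point: if every item is meant to be rated, the sentence should say so, and if the form separates the two, the sentence misdescribes it.

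Second, attribution might be informative. If children correctly recognise effects of the current, filtering would sharpen the contrast. That is possible, but a filtered record cannot distinguish accurate attribution from a guess of arm. Recording relatedness separately keeps that information without losing the rest.

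Three stronger readings are tempting and are not supported:

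- *Real effects are lost.* This follows only on the literal reading, and only for symptoms that the child does not attribute to tDCS.
- *The arms are compared on beliefs about allocation.* Participants are blinded, and Step 4 shows a 2.4-point shift against a standard error of about 8.6 points under modest unblinding. The guess of arm is asked only at one year, so there is no check at the time of the ratings, but that does not show that blinding fails.
- *This is the trial's only safety comparison.* The CDI-2, MASC-2, CBCL and YSR cover mood, anxiety and attention at baseline, end of treatment and every follow-up. They are analysed by arm and carry no relatedness condition. A sustained excess would show there. They would not catch a brief effect after a session.

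**Conclusion.** The point holds as a defect of wording with a real consequence if the wording is followed. The scoring sentence restricts the rating to symptoms related to tDCS, names only the blinded participant to judge this, and sits beside a Safety considerations section that states no such limit yet relies on the same questionnaire. Under the literal reading, non-specific symptoms would be under-recorded and the absolute active-versus-sham difference diluted. In the assumed cases, with half to 30% of symptoms attributed, power falls from 52% to between 24% and 15%, or from 37% to between 19% and 12%.

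These figures are illustrative only. They rest on assumed symptom rates, equal attribution in both arms, and a simple comparison of two proportions that the article does not itself describe. Ratings that follow the perceived arm are a further risk only if blinding fails. The primary outcome and the sample size are not affected.

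**What to change.** In the Safety and tolerability questionnaire section:

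1. State that every listed symptom is graded for intensity after each session and at each follow-up, whatever its perceived cause.
2. Record the participant's view of its relation to tDCS as a separate item.
3. Base any comparison of tolerability between arms on the all-cause grades, with perceived relatedness reported descriptively.
4. Bring the Safety considerations section into line, so that both describe the same unfiltered record.

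If the cited form already separates intensity from relatedness, only the wording needs correcting. Otherwise the cost is one extra item on an existing form. Raw symptom rates will look higher in both arms, because background symptoms are counted; the sham arm is there to put them in context.

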### Outcomes measures

#### Primary outcome measure

We believe that active tDCS, coupled with TAU, will enhance outcome of traditional treatment and will have a substantial impact on symptoms recovery of AN.

The primary end-point of the study is significant improvement on AN psychopathology at T1, assessed as changes in EDI-3 ED-specific (EDRC score).

#### Secondary outcome measures

Secondary psychological outcome measures will be collected at T1, T2, T3, T4 and T5, physiological outcome will be collected at T1, T2 and T4 and only BMI also at T3 and T5, instead neurophysiological outcome measures will be collected only at T1.

Improvement on the other EDI-3 composite scores, EAT-26 total score, BUT-GSI, and CBCL 6–18, YSR 11–18, MASC-2 and CDI-2 subscale’s t-scores, will be considered as secondary psychological end-points.

Possible reduction of left and right hemisphere baseline differences in TEPs, in SICI/ICF and SAI protocols, and increase MEP amplitude in iTBS protocol will be considered as neurophysiological secondary end-points.

Finally, reduction in the CAR, CAR AUCg and AUCi and improvement in nutritional state and BMI, which have normative data for age and sex, will be adopted as secondary physiological end-points.

See Table 1 for details on the outcome measures.

**Table 1. Tab1:** Outcome measures.

Primary outcome measure	Secondary outcome measures	
EDRC score (EDI-3)	Psychopatological	IC, IPC, APC, OC, GPMC scores (EDI-3) EAT-26 total score BUT-GSI CBCL 6–18 subscale’s t-scores YSR 11–18 subscale’s t-scores MASC-2 subscale’s t-scores CDI-2 subscale’s t-scores
	Neuropsysiological	TEPs, SICI/ICF and SAI protocols MEP amplitude in iTBS protocol
	Physiological	CAR, CAR AUCg and AUCi Nutritional state and BMI

*APC* Affective problems, *BMI* Body Mass Index, *BUT* Body Uneasiness Test, *CBCL 6–18* Child behavior checklist for ages 6–18, *CDI-2* Children’s depression inventory—second edition, *AUCg* Cortisol area under the curve relative to the ground, *AUCi* Cortisol area under the curve with respect to the increase, *CAR* Cortisol awakening response, *EAT-26* Eating Attitudes Test, *EDI-3* Eating Disorder Inventory, *EDRC* Eating Disorder Risk, *GPMC* General Psychological Maladjustment, *GSI* global severity index, *IC* Ineffectiveness, *IPC* Interpersonal problems, *MEPs* Motor-Evoked Potentials, *MASC-2* Multidimensional Anxiety Scale For Children—second edition, *OC* Overcontrol, *SICI/ICF* Short intracortical inhibition and facilitation, *SAI* Short-latency afferent inhibition, *iTBS* Theta burst stimulation, *TEPs* TMS-evoked potentials, *YSR 11–18* Youth Self-Report for Ages 11–18.

